### Enrolment, consent and randomization

2.11

Consecutive STEMI patients will be screened following referral to the CCU and on arrival at the hospital. Patients will be considered eligible according to the presence of inclusion criteria and absence of exclusion criteria. Screening will be performed by the attending cardiologist and/or research nurse; the final decision as to whether a patient is eligible to be included in the study will be made and documented by the treating cardiologist. Anterior STEMI patients will be assigned a screening log number. Baseline characteristics and the reason(s) for not being included will be recorded in a screening log database; no follow-up information will be recorded. Patients who are screened and who give informed consent will be recorded in an electronic case report form (eCRF). Patients who are initially eligible but who subsequently become ineligible (such as on angiographic grounds) will not proceed in the study and will become screen failures. Rarely, patients may be treatment allocation failures (such as for logistical reasons); their data will still be recorded in the eCRF.

Because of the need for emergency treatment, delays to obtain full written informed consent in the standard way is not appropriate. Based on experience in prior studies, initial verbal consent is proposed. This approach is in line with contemporary evidence [17], feedback from experts with lived experience and international practice guidelines [8,17]. Patients both fulfilling all inclusion criteria and no exclusion criteria and sufficiently able to understand information about the study (including the potential for benefit and known risks) would be eligible to participate and invited to give verbal informed consent by the attending cardiologist performing primary PCI.

Discussion of the study will take place in the presence of catheter laboratory staff and will cover all points listed in an approved Short Patient Information Sheet. If the patient agrees to participate, then a form to this effect will be signed by the attending interventionalist. Eligibility will be reviewed during primary PCI, reaffirmed at the end of the primary PCI and documented by a study clinician in the medical notes and/or eCRF.

On returning to the ward after completion of primary PCI and study assessments in the catheter laboratory, the patient is to be provided with a full Patient Information Sheet and invited to provide written consent. This must be obtained within 24 h of admission or prior to transfer to base hospital if planned. When this is not possible (perhaps because of clinical deterioration), consent may be delayed and obtained when this becomes feasible. No further study assessments can be performed until written informed consent is obtained.

### Primary PCI

2.12

This is to be performed with radial arterial access. Antiplatelet therapy and systemic anticoagulation with unfractionated heparin as recommended by clinical guidelines [8]. The target activated clotting time (ACT) during primary PCI is >250 s.

### Following randomization

2.13

#### Blinding

2.13.1

Blinding measures will be implemented. The participant will not be advised of treatment assignment. Conscious sedation will be maintained using midazolam and morphine to ensure patient comfort, as in standard care. The participant will be invited to listen to music of their choice using headphones. The effectiveness of blinding will be assessed by prospectively recording the participants' response to treatment group assignment.

### Study assessments (Fig. 1)

2.14

Participants in both groups will be assessed with screening assessments of inclusion and exclusion criteria, ECG confirmation of anterior STEMI and measurement of left ventricular end-diastolic pressure (LVEDP).

**Fig. 1 f0005:**
[figure not shown]
Flow diagram of the protocol.

Vital signs will be continuously monitored in the catheter laboratory as per standard care: blood pressure, heart rate, rhythm, blood pressure, %O_2_ saturation and ECG. ABGs and Killip Class will be checked at half hour intervals. Arterial blood gas samples provide PaO_2_ (inclusion criterion) and will be sampled before starting SSO_2_ therapy, and again at 30 and 60 min.

At the end of primary PCI, and again after SSO_2_ therapy or control, a limited (2 projection) coronary angiogram will be undertaken and hemodynamics (heart rate, invasive blood pressure and LVEDP) measured. Coronary microvascular function (index of myocardial resistance, coronary flow reserve, resistive reserve ratio and microvascular resistance reserve) will be assessed using a Pressure Wire X (Abbott Vascular, Santa Clara, California) placed in the left anterior descending coronary artery.

### Intervention group

2.15

The intervention includes SSO2 therapy given for 1 h via a biradial extracorporeal circuit in association with intravenous glycoprotein IIbIIIa inhibitor therapy with tirofiban for up to 12 h.

Contralateral radial access will be established and a 6 or 7F sheath placed for blood draw at a rate of 100 mL/min. Radial artery access will involve passing an 0.035″ (135 cm) to provide support for positioning a longer guiding sheath with a hydrophilic distal coating e.g. Destination, Terumo (6–7 French, 65 cm length), with the distal end positioned in the axillary artery, distal to the origin of the vertebral and mammary arteries.

Blood will pass through the Downstream® System Console (ZOLL Circulation Inc); hyperbaric blood will be returned via the contralateral radial artery into the left main coronary artery using a 5 French diagnostic catheter (Impulse, Boston Scientific). SSO_2_ therapy will continue for 60 min. Therapeutic anticoagulation will be maintained with a target ACT >250 s, measured every 15–20 min. Intravenous glycoprotein IIb/IIIa inhibitor therapy will be given during SSO2 therapy and continued for up to 12 h afterwards.

### Control group

2.16

Participants assigned to the control group will receive a mock (sham) experience. Additional radial artery access will not be obtained. Auto-perfusion is not proposed. The contralateral wrist will receive local anesthetic and manual pressure will be applied to mimic the experience of sheath insertion. A demonstrator function will be enabled on the console. Normal saline, rather than glycoprotein IIb/IIIa inhibitor, will be given intravenously for all controls and continued for up to 12 h.

### Research blood sampling

2.17

These will be taken at baseline (before coronary angiogram, pre-PCI, pre-randomization, pre-SSO_2_), 75 min after initiation of SSO_2_ or control therapy, 24 h ± 4 h, 2–5 days (at the time of CMR imaging) and at 3 months (on attending for CMR scanning). Blood samples will be saved for future research analyses. High sensitivity troponin I (hsTnI) and NT-proBNP will represent surrogate outcomes for prognosis. Blood samples will be saved for future research analyses including measures of inflammation (hs-CRP, IL-6, ST2), vascular injury (ICAM, VCAM), myocardial infarction (hsTnI), coagulation (fibrinogen, vWF, tPA). A PAXGene tube will be collected for gene pathway analysis.

### Coronary angiography and microcirculatory function tests

2.18

Analysis of angiographic images will proceed in a blinded manner using standardized core laboratory methods. Assessment of the following will be made at the end of primary PCI and following completion of treatment assignment: TIMI flow and thrombus grades in the culprit artery, as well as intraprocedural thrombotic events (IPTE), TIMI frame count and blush grade. Coronary microvascular function will be assessed, as above, in all patients at the end of standard care primary PCI and again following completion of treatment assignment using a Pressure Wire X (Abbott Vascular, Santa Clara, CA) placed in the left anterior descending coronary artery.

### Cardiovascular magnetic resonance imaging

2.19

This will be conducted in line with standard clinical practice within 2–5 days of randomization and again at 3 months using a 1.5 Tesla scanner (Siemens MAGNETOM Avanto, Erlangen, Germany) and a standardized CMR protocol. The imaging protocol will include localizers, cine imaging for cardiovascular dimensions and function including long axis left ventricular imaging e.g., 4 and 3 chamber acquisitions, aortic cine and flow sequences, short-axis planes through the left ventricle (basal, mid-ventricular and apical) for T1-mapping, T2 and T2* mapping (mid-LV only) before administration of gadolinium contrast media, rest- perfusion imaging, short axis cine for LV function, then late gadolinium enhancement imaging and finally postcontrast myocardial T1 mapping. Infarct characteristics, including assessment for microvascular obstruction (MVO) and intramyocardial hemorrhage (T2* <20 ms) (binary yes/no and % LV mass) will be quantified.

Rest perfusion imaging of the 4-chamber and three short axis slices (base, mid and apex), will be acquired following intravenous injection of half-dose gadolinium-based contrast (Gadovist, Bayer) 0.05 mmol/kg 4 mL/s with 30 mL saline flush. Full-dose gadolinium contrast media will then be administered (Gadovist 0.15 mmol/kg at 4 mL/s with 30 mL saline flush) 10–15 min before late gadolinium enhancement imaging (3 long axis views, and short axis stack) acquired using phase-sensitive inversion recovery pulse sequence and free-breathing motion corrected technique.

#### Stress perfusion CMR

2.19.1

This will be performed at 3 months follow-up. Patients will be asked to abstain from caffeine-containing beverages or foodstuffs for 24 h and vasoactive medications for 48 h prior to the CMR examination. Vasodilator stress will be achieved by intravenous infusion of adenosine at a dose of 140 μg/kg/min for 4 min (increased to 210 μg/kg/min for a further 2 min if no symptoms or <10 % heart rate increase). Splenic switch-off will retrospectively be confirmed during image analysis to assess for adequate stress. At peak stress, a gadolinium-based contrast agent (Gadovist, Bayer Healthcare) will be injected at 4 mL/s at a dose of 0.05 mmol/kg. Resting first-pass myocardial perfusion will be performed at least 10 min later.

### CMR imaging analysis

2.20

Scans will be reviewed and reported by an imaging cardiologist blind to treatment group assignment using commercially available software (CVI42, Circle Cardiovascular Imaging, Calgary, Canada). Left ventricular (LV) volumes and function will be analyzed using manual planimetry. LV volumes at end-systole and end-diastole indexed to body surface area will be assessed at 2–5 days and again at 3 months. LV end-systolic volume index (LVESVI) is prespecified as a measure of LV remodeling and an increase in LVESVI at 3 months from baseline will be taken as a measure of adverse LV remodeling. Late gadolinium enhancement will be reported (17 segment model) with scores of 0 (no hyperenhancement), 1 (1 %–25 % extent), 2 (26 %–50 %), 3 (51 %–75 %), or 4 (>75 %). Size of myocardial infarction (% of LV mass) will be reported as will % myocardial salvage and the presence of myocardial hemorrhage. Incidental findings identified will be referred for interpretation by a radiologist and managed according to standard care. Automated quantitative pixel-mapping of myocardial blood flow will be performed using the Kellman Gadgetron framework supported by Siemens Healthcare.

### Health status

2.21

These will be assessed using patient reported outcome measures (PROMS) during follow-up, including the EQ5D-5 L, Duke Activity Status Index (DASI) and Kansas City Cardiomyopathy (KCCQ) questionnaires.

### Adjudicated adverse events

2.22

Follow-up assessments for adverse events will be performed by research staff blinded to baseline data and randomization. Contacts will involve in-person visits, telephone follow-up, or review of electronic health records. Clinical events identified as potentially relevant are to be assessed by a blinded Clinical Event Committee blinded to both baseline data and randomization, according to prespecified charter. The committee will be independent of the investigators, funder, and sponsor.

During the initial hospital stay, adverse events of interest will include peripheral and cerebrovascular ischemic events and bleeding events, defined by Bleeding Academic Research Consortium (BARC) [18].

Standardized cardiovascular and stroke endpoint definitions will be used [19]. Health outcomes will include death, and cardiovascular events including MI, heart failure, stroke/TIA, and bleeding. Data on health outcomes will be collected during index admission and after hospital discharge by clinical review for all patients at 3 months and by electronic health record checks at 12 months and at the close of the study (or by letter or patient review as appropriate to ensure complete data, including for quality of life). Electronic case record linkage using the Community Health Index (CHI) number in Scotland will allow tracking of all deaths and hospitalizations (and their causes). Functional status will be assessed using validated measures: EQ-5D-5L, DASI and KCCQ.

### Assessment of health economics

2.23

An economic evaluation will compare usual care (as defined by the control group arm of the trial) with usual care-plus-SSO_2_ therapy. Resource use data will be collected for: days in hospital (including in each of the following ward types: intensive care, coronary care, and general cardiology ward), SSO_2_ therapy, medications given to the patient (e.g. glycoprotein IIb/IIIa), costs of procedures (including the duration of PCI, need for repeat procedures, use of implantable defibrillators and repeat hospital admissions related to the original STEMI event). Complications will be captured through added length of stay or through subsequent procedures carried out.

### Follow-up

2.24

Patient follow-up will begin from the date the first patient is recruited until 12 months after the final patient is recruited.

### Adverse events

2.25

All serious adverse events (SAE) and adverse events of interest will be prospectively assessed and documented for relatedness and severity. In addition, electronic case record linkage will be used to obtain information about health outcomes. These are quality assured systems made possible by electronic registration of all deaths and hospitalizations (and their causes).

#### Periprocedural adverse events

2.25.1

Intra-procedural thrombotic events (IPTEs) are of interest and include new or worsened coronary thrombus, vessel closure, no reflow, slow flow and/or distal embolization. Peripheral ischemic events (cerebrovascular, peripheral) will also be documented.

#### During initial hospitalization

2.25.2

Patients will be assessed as per study schedule by the research team for serious adverse events (SAEs), adverse events of interest (i.e. peripheral and cerebrovascular ischemic events) and bleeding events, defined by Bleeding Academic Research Consortium (BARC).

#### During follow-up

2.25.3

Health outcomes will include death, and cardiovascular events including MI heart failure, stroke/TIA and bleeding. Data on health outcomes will be collected during the index admission and after discharge from each hospital by a clinic review for all patients at 3 months (including for the follow-up MRI scan) and by electronic health record checks at 12 months and at the close of the study (or by letter or patient review as appropriate to ensure complete data, including for quality of life).

### Statistical considerations

2.26

Analyses will be descriptive, aiming to estimate between-group differences with 90 % confidence intervals. *P*-values will be reported, but the results will be interpreted in terms of the magnitude of estimated between-group differences, over time where applicable. Analyses will be according to intention-to-treat principles, supported by as-treated analyses. Missing data will not be imputed initially, but multiple imputation may be applied as sensitivity analyses.

### Primary analysis and sample size calculation

2.27

The primary outcome is the within-participant change in the plasma concentration of NTproBNP measured at baseline, 24 h, days 2–5, and 3 months. The primary analysis will involve a between-group comparison of the log-transformed NTproBNP. In the MR-MI cohort study of 343 patients presenting with acute STEMI in the NHS Golden Jubilee hospital with follow-up assessments (cardiac MRI, NTproBNP) at 5 days and 6 months post-STEMI [4–6], a linear regression model of follow-up log NT-proBNP, adjusted for baseline, had a residual SD of 0.87. If a minimum of 51 randomized (2:1) participants have complete data, then with 80 % power and a 2-sided alpha of 0.05 the minimum detectable difference in SD units for the primary outcome is 0.85. To take account of incomplete SSO2 therapy and/or missing data for the primary outcome at baseline, then the minimum sample size is 56 patients, randomized 2:1 to the intervention versus control groups.

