### Primary outcome

2.5

The plasma concentration of NT-proBNP at baseline (prior to primary PCI), and at 24 h, 2–5 days, and 3 months after primary PCI.

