Increasing the number of sampling time points for the primary outcome mitigates the negative effects of missing data. For example, missing data are particularly problematic for paired evaluations (i.e. ×2, baseline and follow-up), which is the usual approach adopted for cardiac MRI, since missing data for just one sample rules-out paired comparisons, or any assessment of efficacy if no follow-up data are collected. Since the sample size of our trial is modest (*n* = 56), missing data would have a disproportionate effect, hence, this is mitigated by adoption of multiple sampling time points for the primary outcome.

Fourth, the final follow-up assessment is scheduled for 3-months. This time point takes account of the natural history of left ventricular remodeling post-MI (mostly established by 3-momths) balanced against the reducing likelihood of participant retention as follow-up is extended and increased costs of coordinating a clinical trial as the study duration is prolonged.

Finally, the fifth novel study design feature is participant blinding. This is achieved by implementation of a bespoke sham experience in the catheterization laboratory that is intended to mitigate the influence of bias on patient reported outcomes measures of health-related quality of life after treatment assignment. Data from this study are intended to inform a larger randomized study with clinical endpoints.

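### Section 2.27 counts a missing baseline NT-proBNP as a loss; read with 2.26, this implies losing randomized patients who have usable follow-up samples, which section 2.5 would allow to be kept

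*Protocol article*

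**What the plan says.** Protocol article, section 2.27 (Primary analysis and sample size calculation): "The primary outcome is the within-participant change in the plasma concentration of NTproBNP measured at baseline, 24 h, days 2–5, and 3 months". The analysis is described only as follows: "The primary analysis will involve a between-group comparison of the log-transformed NTproBNP". The variability used for sizing comes from a regression in an earlier cohort that was "adjusted for baseline, had a residual SD of 0.87". With 51 patients randomized 2:1 and complete data, the stated minimum detectable difference is 0.85 SD at 80% power and two-sided alpha 0.05. The total is then raised for two reasons taken together, incomplete SSO2 therapy and/or "missing data for the primary outcome at baseline, then the minimum sample size is 56 patients".

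Section 2.5 (Primary outcome) defines the outcome without a change: "The plasma concentration of NT-proBNP at baseline (prior to primary PCI), and at 24 h, 2–5 days, and 3 months after primary PCI".

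Section 2.26 (Statistical considerations): "Analyses will be according to intention-to-treat principles, supported by as-treated analyses". It adds: "Missing data will not be imputed initially, but multiple imputation may be applied as sensitivity analyses".

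Section 2.17 (Research blood sampling) gives one baseline sampling time, before angiography and before randomization.

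The Discussion justifies serial sampling as protection against missing primary-outcome data. It says of an ordinary before-and-after pair that "missing data for just one sample rules-out paired comparisons".

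**The concern.** A change from baseline needs a baseline, and there is only one. A patient who misses a follow-up visit still has other follow-up samples to offer. A patient who misses the baseline loses all three changes at once, even with the 24 h, 2–5 day and 3-month values in hand. The same holds for a regression adjusted for baseline when nothing is imputed.

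The plan expects some missing baselines and budgets for them by recruiting extra patients. The sample named in the allowance is therefore the one that the Discussion's argument for serial sampling does not protect.

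At stake are some avoidable loss of precision and a primary analysis set smaller than the randomized set, in a trial that declares intention-to-treat principles and describes its own size as modest. The loss is not necessary. Because the baseline sample precedes randomization, its expected value is the same in both arms, and follow-up values can be compared without it.

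**Working it through.** **Inputs from section 2.27.** 51 patients with complete data, 2:1, so 34 and 17; two-sided alpha 0.05; power 80%; detectable difference 0.85 SD; total 56.

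**Assumed.** The correlation r between baseline and follow-up log NT-proBNP is not in the document. The range 0.2–0.7 is used.

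**1. Reproduce the stated figure.** Standard error of the contrast in SD units: √(1/34 + 1/17) = 0.297. With the noncentral t on 49 degrees of freedom, the detectable difference at 80% power is 0.849 SD, and power at 0.85 SD is 80.1%. The stated figure holds.

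**2. Size of the allowance.** 56 − 51 = 5, and 5/56 = 8.9%. The split between the two reasons is not given, so the number of missing baselines within the allowance is anywhere from 0 to 5.

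**3. Worth of a patient without a baseline.** Adjusting for baseline reduces the outcome variance by the factor 1 − r². A patient without a baseline keeps the full variance, so the relative weight is 1 − r². Take the largest case, all 5 lacking only the baseline and split 2:1. The effective size is then 51 + 5(1 − r²). For example, r = 0.7 gives 51 + 5 × 0.51 = 53.55.

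| Handling | Effective size | Standard error | Detectable difference (SD) | Power at 0.85 SD |
|---|---|---|---|---|
| Five left out | 51 | 0.297 | 0.85 | 80.1% |
| Kept, r = 0.7 | 53.6 | 0.290 | 0.83 | 82.0% |
| Kept, r = 0.5 | 54.8 | 0.287 | 0.82 | 82.9% |
| Kept, r = 0.3 | 55.6 | 0.285 | 0.81 | 83.5% |
| Kept, r = 0.2 | 55.8 | 0.284 | 0.81 | 83.6% |
| Upper bound, all 56 at full weight | 56 | 0.283 | 0.81 | 83.8% |

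Leaving the five out makes the variance of the contrast larger by 53.55/51 − 1 = 5% (r = 0.7) to 55.8/51 − 1 = 9% (r = 0.2). This treats one follow-up contrast and gives no extra credit for having three follow-up times.

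**4. The two definitions side by side.** Under 2.27 (change), a patient with three follow-up values and no baseline has no outcome. Under 2.5 (concentration at each time), the same patient has three outcome values. The no-imputation sentence in 2.26 removes the patient under the first reading and not under the second.

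**The case against.** Much of the case on the other side stands.

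- **Exclusion is not written.** A reader might infer that the plan drops these patients. No section says so. Sizing on complete cases is ordinary conservative planning, and a sample-size allowance is not an analysis-set rule. Exclusion follows only from combining the change definition, the complete-data count and the no-imputation sentence.
- **The model is not named.** Section 2.5 and the bare description of the primary analysis leave room for a longitudinal model, and a statistical analysis plan may specify one. The cohort regression supplies a standard deviation; it does not prescribe the primary model. What remains is that the article's own definitions differ and give different answers for the same patient, and that 2.27 leans towards losing that patient.
- **The allowance is shared** with incomplete SSO2 therapy, so five missing baselines is a ceiling within the plan and not its forecast.
- **The mitigation claim is partly limited already.** The Discussion introduces it in terms of missed follow-up visits. The paragraph after that speaks of missing data generally and does not set aside the baseline.
- **Bias or a failed design might be inferred; neither is supported.** The baseline is taken before randomization, so its absence should not depend on arm, and a comparison restricted to patients with a baseline is still a randomized one. A reader might also suspect many missing baselines, because the sample precedes angiography while consent (section 2.7) is sought during or at the end of PCI. If 10 of 56 were lost, power would be 75.7% and the detectable difference 0.90 SD. The document gives no such rate, so this is illustration only.

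**Conclusion.** The point holds in a limited form. As worded, sections 2.26 and 2.27 imply that a randomized patient without the baseline sample is lost to the primary analysis despite usable follow-up values, and the serial-sampling argument does not cover that loss. Section 2.5 points the other way, so the two definitions need reconciling.

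The size is modest: at most 5 patients within the plan's allowance, worth 0.02–0.04 SD in the detectable difference and about 2 to 4 percentage points of power. This rests on the assumed correlations and on all 5 losses being missing baselines; with fewer, the gain shrinks towards nil. Even with all 5 lost, the stated 0.85 SD is met. The reason to act is that the gain is nearly free and brings the primary analysis closer to the declared intention-to-treat principle.

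**What to change.** 1. Give sections 2.4, 2.5 and 2.27 one definition of the primary outcome.
2. In 2.27, specify a longitudinal model of log NT-proBNP with the baseline value as one of the responses and a baseline mean common to both arms (constrained longitudinal data analysis). Every randomized patient with at least one value can then enter. The model needs no imputation, so it fits 2.26 as written; it assumes that data are missing at random.
3. State in 2.26 or 2.27 that a missing baseline is not a reason for exclusion from the intention-to-treat primary analysis.
4. If a baseline-adjusted regression is preferred, fill the missing baseline covariate with the mean over both arms, ignoring allocation, and amend the no-imputation sentence in 2.26 to permit this.
5. If the change score is kept, limit the Discussion's claim about serial sampling to missing follow-up samples.

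The cost is wording and a different model call, with no extra patients, samples or visits.
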